### Data management

All data collected on paper forms will include only the participant’s ID number. Paper forms will be transferred securely in study vehicles to the storage site where they will be kept in locked filing cabinets within locked offices. Electronic data capture using the ACASI program will also only include participant ID numbers and be stored on encrypted drives.

### Data analysis

The analysis will be done using an intent-to-treat approach. Mixed effects regression models will be estimated for each mental/behavioral health outcome. Models will include fixed effects of treatment group, time, and a group × time interaction term. Random effects will include client ID and counselor ID. There will be two sets of analyses. First, we will conduct a superiority analysis, in which each of the CETA arms (CETA and T-CETA) is separately compared to TAU. Second, we will conduct a non-inferiority analysis in which we will compare the outcomes between the CETA and T-CETA groups.

The total number of AYA participants will be *N* = 400. We conducted power calculations for each of the three primary outcomes for which AYA will be enrolled in the study (trauma symptoms, internalizing symptoms, externalizing behaviors). All three required similar sample sizes; trauma symptoms required the largest sample size and are presented here. Based on a previous study with AYA using the same trauma symptom scale as this study (CPSS) [73], we hypothesize a baseline mean value of approximately 19.0 and a standard deviation of 13. For the superiority analyses, in which we will separately compare each CETA condition (in-person CETA and T-CETA) to the TAU control, we will assume an alpha = 0.025 to account for two comparisons. Further assuming power = .80 and an expected minimum effect size of each CETA condition compared to TAU of 0.5, we would require 78 persons per arm. For the non-inferiority analysis, in which we will compare the two CETA conditions to each other, we assume an alpha = 0.05, power = 80%, and a non-inferiority margin of 4.7, which is equivalent to one-third of the anticipated standard deviation. Previous studies have indicated that differences in the outcomes that are less than one-third of the standard deviation are considered not practically meaningful. Based on these assumptions, we would require 114 in each CETA arm for the non-inferiority comparison. Using the more conservative estimate for the CETA conditions (*N* = 114 each) and the estimate for the TAU (*N* = 78) yields a total sample size of *N* = 306. Assuming 20–25% attrition based on previous studies, we have inflated the final sample size to *N* = 400 (*N* = 100 TAU, *N* = 150 CETA, *N* = 150 T-CETA).

The incremental cost-effectiveness analysis will compare the cost-effectiveness of CETA and T-CETA relative to TAU. We will first derive quality-adjusted life years (QALYs) from health utility reported at each follow-up time point by AYA and then estimate the differences in the mean QALYs gained per treatment condition over study follow-up using the mixed effects models detailed above. We will then divide incremental QALYs gained under CETA and T-CETA by the incremental cost of each relative to TAU from the economic perspective of the healthcare provider (i.e., payer’s perspective) to estimate the primary cost-effectiveness outcome: incremental cost per QALY gained. Sensitivity analyses will be undertaken to examine the uncertainty around the cost-effectiveness estimates, and further interpreted using cost-effectiveness acceptability curves that reveal to decision-makers the probability of the intervention being cost-effective compared to the alternative, given different (implicit monetary) values placed on incremental improvements in the outcome measurement and QALYs. Cost-effectiveness acceptability curves will be based on bootstrapped regressions (to account for non-normally distributed data) of the study group upon net benefits, controlling for clusters.

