### Screening and baseline assessment

The screening portion of the baseline assessment consists of demographic information, internalizing and externalizing symptoms, and post-traumatic stress. Screening instruments will be administered using the audio computer-assisted self-interviewing (ACASI) system. Participants can navigate through the questionnaires themselves using a laptop computer while listening to the questions through headphones and seeing the question and response options on the screen. A research assistant will be positioned nearby in case the participant has any difficulty. We have used ACASI extensively with AYA populations in Zambia and found it to be an acceptable and feasible approach for measuring mental and behavioral health outcomes [69]. All measures included in the ACASI have previously been used by our team with similar study populations and are available in English, Bemba, and Nyanja [35, 68–72].

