### Outcomes

The primary outcomes in the trial will be AYA trauma symptoms (as measured by the CPSS), internalizing symptoms, and externalizing behaviors (both measured by the YSR) administered via ACASI as described in the “Screening and baseline assessment” section. Secondary outcomes among AYA, also administered via ACASI, include substance use, which will be measured with the Alcohol, Smoking, and Substance Involvement Screening Test (ASSIST) [67, 77] and aggression/violence as measured by the Youth Victimization Scale [78]. Outcomes are assessed at baseline, post-treatment completion (approximately 3–4 months post-baseline for TAU participants), and 6 months post-treatment completion (approximately 9 months post-baseline for TAU participants). The primary time point is post-treatment.

In addition to AYA outcomes, we will collect preliminary data on counselor and trainer competency, fidelity, and knowledge. This will be collected at various points throughout the study through standardized role-plays and CETA knowledge tests. Mixed methods interviews will be conducted among clients, counselors, and trainers to explore the acceptability and feasibility of CETA training and delivery. We will also collect data on health utility among AYA using the EuroQol 5-Dimensions for Youth (EQ-5D-Y) [79, 80] to inform the cost-effectiveness analyses. In all, AYA participants will be engaged in the study for approximately 9–12 months.

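### The stated mixed model leaves baseline means free in each arm and does not adjust for baseline: an avoidable loss of precision, not a bias

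*Protocol article*

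**What the plan says.** The Data analysis section of the protocol article fixes one model for every mental and behavioral outcome: "Models will include fixed effects of treatment group, time, and a group" by time interaction. It adds: "Random effects will include client ID and counselor ID". It states neither a baseline covariate nor a constraint that the arms share a baseline mean.

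The Outcomes section makes baseline one of the modelled times: "Outcomes are assessed at baseline, post-treatment completion (approximately 3–4 months post-baseline for TAU participants), and 6 months post-treatment completion". It also says: "The primary time point is post-treatment". Under Randomization and blinding, a participant is assigned only after eligibility is settled and the baseline assessment is complete.

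The tested coefficient is not named. For non-inferiority the text says only that "we will compare the outcomes between the CETA and T-CETA groups". The sample size uses a cross-sectional SD of 13 and the statement "we assume an alpha = 0.05, power = 80%, and a non-inferiority margin of 4.7", with the margin described as one-third of the SD, and arrives at 114 per CETA arm.

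**The concern.** With group, time and their interaction as fixed effects, the group main effect gives each arm its own baseline mean. Because randomization comes after baseline, any baseline difference between arms is chance. The model spends information estimating a quantity whose true value is known to be zero, and makes no use of the baseline score to explain follow-up variation.

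The same model serves all three primary outcomes and both sets of comparisons. The cost is wider confidence intervals than the collected data allow, and it matters most for the non-inferiority test, which sets the size of the CETA arms. The sample size rests on the SD of a score at one time. That equals the variance the interaction delivers only when rho is 0.5, so under that reading planned and delivered power need not agree.

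**Working it through.** **Inputs from the article.** SD 13; margin printed as 4.7 and described as SD/3; alpha 0.05 (sidedness not stated); power 80%; 114 per CETA arm; 150 randomized per CETA arm; attrition 20–25%.

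**Assumptions.** rho is not in the article; I use 0.3 to 0.7. SDs are equal at all visits, the correlation structure is compound symmetry, data are complete unless stated, the true difference is zero, and counselor clustering is ignored.

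**Step 1: reproduce 114.** With one-sided alpha 0.05, n per arm = 2 × (1.645 + 0.842)² × (SD/margin)², where the squared sum is 6.183 before rounding.
- Margin 13/3 = 4.33: 2 × 6.183 × 9 = 111.3, so 112.
- Margin 4.3: 2 × 6.183 × 9.140 = 113.02, so 114.
- Margin 4.7: 2 × 6.183 × 7.651 = 94.6, so 95.

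The printed 114 therefore matches a margin of about SD/3 tested one-sided at 5%, not 4.7 with SD 13. A margin of 4.7 is one-third of 14.1, not of 13.

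**Step 2: variance of each contrast, relative to comparing post-treatment scores alone.** Generalized least squares for three visits confirms these factors.

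| Contrast | Factor | rho 0.3 | rho 0.5 | rho 0.7 |
|---|---|---|---|---|
| Group × time (difference in change), free baseline | 2(1 − rho) | 1.40 | 1.00 | 0.60 |
| Post-treatment mean difference, free baseline | 1 | 1.00 | 1.00 | 1.00 |
| Common baseline mean, or baseline as covariate | 1 − rho² | 0.91 | 0.75 | 0.51 |

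Share of variance removed by the third option:
- Against the interaction: 1 − (1 − rho²)/[2(1 − rho)] = (1 − rho)/2, i.e. 35%, 25%, 15%.
- Against the post-treatment difference: rho², i.e. 9%, 25%, 49%.

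For any rho strictly between 0 and 1 the third option has the smallest variance.

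**Step 3: non-inferiority power at 114 per arm, one-sided 5%.** Power = Φ(margin / [13 × √(2v/114)] − 1.645), with v the factor above.

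| rho | Interaction, margin 4.33 | Adjusted, margin 4.33 | Interaction, margin 4.7 |
|---|---|---|---|
| 0.3 | 68.5% | 84.0% | 74.6% |
| 0.4 | 74.3% | 86.5% | 80.1% |
| 0.5 | 80.8% | 89.6% | 86.1% |
| 0.6 | 87.9% | 93.3% | 92.0% |
| 0.7 | 94.6% | 97.0% | 97.0% |

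The post-treatment mean difference (v = 1) gives 80.8% with margin 4.33 and 86.1% with 4.7 at every rho.

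**Step 4: break-even rho for 80% power with the interaction.** Set v* = 114 × margin² / (2 × 169 × 6.183); then rho* = 1 − v*/2.
- Margin 4.33: v* = 1.024, rho* = 0.49.
- Margin 4.7: v* = 1.205, rho* = 0.40.
- With 150 randomized, 24% losing both follow-ups and their baselines kept in the model: 0.45 (margin 4.33) or 0.35 (margin 4.7).
- One-sided 0.025 with margin 4.7, complete data: 0.525. That alpha does not reproduce 114 (it gives 121).

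**The case against.** **The contrast is not named.** The same model yields the arm difference in fitted means at post-treatment, which is the stated primary time point. That contrast has factor 1.00, matches a sample size built on SD 13, and keeps the planned power. This objection stands. A reader might infer that the plan tests a difference in change and so misses its non-inferiority power; the article does not say so, and the shortfall exists under only one of two readings.

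**Selection on baseline.** A reader might argue that rho must be low because the eligibility scores are also the baseline scores: "The screening portion of the baseline assessment consists of demographic information, internalizing and externalizing symptoms, and post-traumatic stress". This does not work. Selection on baseline lowers the correlation by shrinking the baseline SD, and 2(1 − rho) requires equal SDs. Under a linear regression the slope of follow-up on baseline is unchanged, and change beats post-only when that slope exceeds 0.5. In a simplified check (bivariate normal, mean 19, SD 13, CPSS at least 12, unselected rho 0.5, ignoring entry through the two YSR scales) the correlation falls to 0.38. The variance of change is nevertheless 0.87 of 13², not the 1.24 that 2(1 − 0.38) would give, and power with margin 4.33 is 85%. The article offers no basis for a rho below 0.5.

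**An article condenses the plan.** Covariates and exact contrasts are often left to the analysis plan, and this specification is common and valid. That rules out criticizing missing detail. It does not remove the point, because the article does state a model, and a better one is available from data already collected.

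**Conclusion.** The point holds as a loss of efficiency. The estimator is unbiased and type I error is unaffected; the article does not contradict itself on the model.

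The gain from adjustment does not depend on which contrast is intended; only its size does: 35% to 15% of the variance for the interaction and 9% to 49% for the post-treatment difference, as rho runs from 0.3 to 0.7. These figures rest on an assumed rho, equal SDs and complete data.

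A power shortfall is not established. It would arise only if the interaction is the test and rho is low, and the threshold moves with the margin. No threshold should be quoted as fixed until 4.7, SD 13 and 114 are reconciled. Above the threshold a difference in change has more power than planned. This is a free improvement, not a correction of an error.

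**What to change.** Name the between-arm difference at post-treatment as the primary contrast for each comparison, and estimate it in one of two ways:
- Keep the longitudinal model with visit as a factor, constrain the baseline mean to be equal across arms, and include group-by-visit terms only at the two post-baseline visits.
- Model the post-baseline scores only, with baseline score and baseline-by-visit as covariates.

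Separately, reconcile the margin, the SD and the 114, and state whether alpha is one- or two-sided, before quoting any power for the chosen contrast.

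The cost is a line or two in the model specification, settled before analysis. No new data or extra participants are needed.

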### Randomization and blinding

Each participant will be assigned a unique ID number by the research assistant during the screening/baseline assessment. Randomization will occur at the individual AYA level and be stratified by site. Following the determination of eligibility and completion of the baseline assessment, the research assistant will communicate the ID number to a study staff based at research headquarters who will not interact with study participants. This study staff will maintain a randomization sequence that will be developed a priori by a US-based research staff. This list will not be available or viewable to data collectors in Zambia. The list will have a sequence of treatment assignments (CETA or T-CETA or TAU) in random order, stratified by site, produced via a random number generator in Microsoft Excel. Randomization will be imbalanced (1.5 CETA: 1.5 T-CETA: 1 TAU) due to the different sample size requirements in the TAU control arm (see the “Data analysis” section). Eligible AYA participants will be assigned a condition based on the next available slot on the randomization list and inform the field staff of the assignment. At this point, the field staff will not be blinded to condition assignment for participants they assess. Eligible AYA clients will be informed immediately of the result of the randomization and appropriate next steps: CETA and T-CETA participants will be told that a counselor will be contacting them within 48 h to set up the first session; TAU participants will be told that the study team will contact them in approximately 3 months to schedule their first post-assessment. The use of ACASI will result in the outcome assessments being blinded; data analysts will also be blind to the intervention status when conducting analyses. Due to the nature of the intervention, neither counselors nor AYA clients will be blinded.

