##### Treatment as usual control

Participants randomized to the TAU condition will be encouraged to continue engaging with support services normally offered in their community, such as those provided by the partnering organization, and the types and utilization of these services will be tracked. Counselors will check in with TAU participants monthly to assess safety; any participant with a safety risk will be contacted by a counselor to complete a safety plan and be monitored. All TAU participants will receive a full course of CETA, if desired, after completion of the active study aims. For all study arms, a dedicated adherence team will be identified at each partner site and overseen by the project manager. Adherence strategies will include regular telephone check-ins, coordination with other site providers, and, if needed, home visits. Following the participation in the trial, participants will be provided a list of available resources in the community and the option to reengage with CETA providers in the area, if needed.

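### The counselor random effect, read as a plain intercept, drops out of the group-by-time contrast, so counselor differences in treatment response are not allowed for and the superiority standard errors may be too small

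*Protocol article*

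**What the plan says.** The Data analysis section of the protocol article gives the model for every mental and behavioral health outcome: "Models will include fixed effects of treatment group, time, and a group × time interaction term", followed by "Random effects will include client ID and counselor ID". The same models serve the two superiority comparisons with TAU and the T-CETA versus CETA comparison. The Outcomes section lists baseline, post-treatment and 6 months post-treatment as assessments, with post-treatment primary.

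On who has a counselor, the Randomization and blinding section says that "CETA and T-CETA participants will be told that a counselor will be contacting them within 48 h". For the control arm, "TAU participants will be told that the study team will contact them in approximately 3 months to schedule their first post-assessment". The Treatment as usual control section adds "Participants randomized to the TAU condition will be encouraged to continue engaging with support services normally offered in their community" and also "Counselors will check in with TAU participants monthly to assess safety". The article does not say which counselor ID, if any, a TAU client carries in the model.

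Counselors number at most 50, and each is trained in both delivery modes (Overview of study design; CETA training). On strata, "Randomization will occur at the individual AYA level and be stratified by site"; site is not among the listed model terms.

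**The concern.** A counselor term is presumably there to allow for clients of the same counselor doing similarly. Such clustering is plausible: the counselors are newly trained lay providers, and the intervention lets each of them choose elements, order and number of sessions. Two features of the stated term keep it from doing this job.

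- **Timing.** Baseline is completed before randomization and before any counselor contact, yet an intercept gives the counselor the same effect at baseline as at follow-up. The effect of interest is a change from baseline, so the intercept subtracts out.
- **Arm.** Counselors can influence response to treatment only in CETA and T-CETA. In TAU a counselor ID would at most identify the person making safety calls, which is a different thing from a treating counselor.

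If counselors do differ in effect, clients of one counselor are not independent at follow-up, and the model treats them as if they were. The SE of each comparison with TAU is then too small and the true type I error exceeds the planned 0.025.

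**Working it through.** **Inputs from the Data analysis section.** SD 13, effect size 0.5, alpha 0.025 per superiority comparison, power 0.80, 78 per arm for superiority, 114 per CETA arm for non-inferiority. The ceiling of 50 counselors is in the Overview of study design.

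**Assumed, because the documents give no value.** ICC of response 0.01 to 0.10; 50, 20 or 12 active counselors with equal caseloads; baseline-to-post correlation 0.5. With that correlation the variance of change is 2 × (1 − 0.5) × 13² = 13², so an ICC means the same on the change scale as on the score scale.

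**Step 1: reproduce the plan's figure.** Two-sided alpha 0.025: n = 2 × (2.241 + 0.842)² / 0.5² = 76.04, so 77; the t-based version gives 77.3, so 78. This matches the stated 78. It is a simple two-sample figure with no allowance for clustering.

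**Step 2: does the intercept cancel?** For client i of counselor j, write the score as fixed part + u(j) + b(i) + error. Post-treatment minus baseline removes both u(j) and b(i). With complete data, the group-by-time estimate is the difference in mean change, whatever the variance of u(j). Mixed-model fits to simulated data agree (12 counselors, a counselor effect arising only after baseline with ICC 0.10, site SD 6). The mean SE was 1.958 with a client intercept alone, with a counselor intercept added, and with site added. SE differences were below 0.0001.

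**Step 3: size of the understatement.** Take 114 CETA against 78 TAU, J counselors, m = 114/J clients each, clustering in the CETA arm only.

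- Design factor: D = 1 + (m − 1) × ICC
- SE ratio, true over model: R = √[(D/114 + 1/78) / (1/114 + 1/78)]
- Actual error: 2 × [1 − Φ(2.2414/R)]
- Power with the correct SE: Φ(0.5/√(D/114 + 1/78) − 2.2414)

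Example with J = 20 and ICC 0.10: m = 5.7 and D = 1.47. Then D/114 + 1/78 = 0.02572 against 0.02159 unclustered, so R = √1.191 = 1.091 and the error is 0.040.

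| J | ICC | D | R | Actual error | Power |
|---|---|---|---|---|---|
| 50 | 0.01 | 1.013 | 1.003 | 0.0254 | 0.875 |
| 50 | 0.05 | 1.064 | 1.013 | 0.0269 | 0.868 |
| 50 | 0.10 | 1.128 | 1.026 | 0.0289 | 0.859 |
| 20 | 0.01 | 1.047 | 1.010 | 0.0264 | 0.871 |
| 20 | 0.05 | 1.235 | 1.047 | 0.0322 | 0.844 |
| 20 | 0.10 | 1.470 | 1.091 | 0.0400 | 0.810 |
| 12 | 0.01 | 1.085 | 1.017 | 0.0275 | 0.865 |
| 12 | 0.05 | 1.425 | 1.083 | 0.0385 | 0.816 |
| 12 | 0.10 | 1.850 | 1.160 | 0.0533 | 0.756 |

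Without clustering the power at these sizes is 0.877. With 120 against 80 (150 and 100 less 20% attrition) the values at ICC 0.10 are nearly the same: R = 1.028, 1.095 and 1.166, and error 0.029, 0.041 and 0.055, for 50, 20 and 12 counselors.

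**Step 4: check by simulation** (20,000 runs, baseline and post-treatment scores; true SD of the estimate against mean model SE, then error).

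- No counselor effect: 1.901 against 1.908, error 0.027.
- 50 counselors, ICC 0.05: 1.947 against 1.937, error 0.027.
- 25 counselors, ICC 0.05: 2.020 against 1.935, error 0.032.
- 12 counselors, ICC 0.05: 2.075 against 1.934, error 0.038.
- 12 counselors, ICC 0.10: 2.250 against 1.961, error 0.054.

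**Step 5: T-CETA versus CETA** (114 per arm, counselors evenly crossed with arm, one-sided 0.05).

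- 25 counselors, ICC 0.05: true 1.72 against model 1.76, error 0.048.
- 12 counselors, ICC 0.10: true 1.73 against model 1.80, error 0.044.
- 25 counselors, ICC 0.05 plus a counselor-by-mode share of 0.02: 1.79 against 1.78, error 0.052.
- 12 counselors, ICC 0.05 plus a counselor-by-mode share of 0.05: 2.10 against 1.80, error 0.082.

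**Step 6: site.** With a constant site SD of 6 left out of the model and no counselor effect, the error was 0.0265, against 0.0266 in the run with no site effect. A constant site effect cancels exactly as the counselor intercept does.

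**The case against.** The article does not use the word intercept, its list of random effects need not be complete, and it is a condensed account of a full protocol that the Data Availability statement offers on request. Covariance structure, coding of the ID in TAU and stratum covariates are often settled there. This stands in part: it makes the point conditional on the plain reading, and it means that the missing site term alone would be no finding. It does not remove the point, because the term as written, in its ordinary meaning, does not do what it is there to do.

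The effect may also be negligible. If all 50 counselors carry cases, the SE is off by under 3% even at ICC 0.10, and at ICC 0 it is right. This stands too.

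Three stronger inferences are tempting, and the documents do not support them.

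- **TAU clients have no counselor ID, so their rows are lost and the comparison with TAU cannot be estimated.** Counselors do contact TAU clients monthly, so an ID could be recorded, and the article does not say that it would be left blank. If TAU were coded as one counselor, that shift would be common to TAU baseline and follow-up and would also cancel.
- **Omitting site makes the SEs wrong.** For the stated contrast a constant site effect changes nothing (step 6). Only a post-score comparison, which the article does not describe, would be affected.
- **The non-inferiority comparison fails in the same way.** Counselors deliver both modes, so a shared counselor effect largely cancels between the arms. That SE is right or slightly too large unless counselors differ by mode.

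**Conclusion.** The point holds in a limited form. As a plain intercept, the counselor term leaves the group-by-time estimate unchanged and its SE practically unchanged. The superiority SEs then carry no allowance for counselor differences in response, and the direction of error is anti-conservative.

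The size depends on two unknowns. It is minor if the full 50 counselors share the caseload, and material if a small number carry it: at 12 counselors and ICC 0.10 the actual error is about twice the planned 0.025. These figures assume equal caseloads, complete data at the evaluable sizes, two visits and a correlation of 0.5. With dropout the cancellation is close rather than exact. For T-CETA versus CETA the concern is confined to counselor-by-mode differences.

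This should be corrected before analysis. It does not show that the planned SEs are wrong.

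**What to change.** - Replace the counselor intercept with a partially nested term: a counselor random effect multiplied by an indicator for a post-baseline visit in CETA or T-CETA. It is zero at baseline and zero throughout TAU.
- State that TAU clients are analyzed as unclustered. Give them a placeholder ID, which the indicator multiplies by zero, so that no TAU rows are lost.
- For T-CETA versus CETA, keep counselors crossed with arm and add a counselor-by-arm random effect at post-baseline visits.
- As a minor addition, include site and site-by-visit as fixed effects, since site is the randomization stratum. A constant site term alone would not change the group-by-time SE.

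The cost is a few sentences of model wording, slightly more complex code and a few degrees of freedom for site. No data beyond the counselor ID are needed. If clustering is present, the corrected SEs will be larger and the power lower, as in the table under step 3; that loss comes from the clustering and is hidden, not avoided, by the present model.

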## Discussion

Scalable systems of care, such as those being tested in this trial, are needed to close the mental health treatment gap in LMIC, particularly for populations at-risk for poor outcomes and low treatment adherence, such as adolescents and young adults. The need for telephone-based mental health services in LMIC has become widely discussed during the COVID-19 pandemic. Significant barriers to scale-up of evidence-based treatments in LMIC include a lack of feasible, sustainable training for local lay providers, and client access to care. This will be the first CETA trial that is specifically designed to evaluate the treatment effectiveness among an adolescent population and the first to feature a technology-based training modality and a telehealth delivery. This study is a first step to build a system of technology-driven training and treatment provision to expand access to evidence-based mental healthcare in Zambia and other LMIC settings. The need for effective, remotely delivered interventions is particularly relevant in the COVID-19 era.

There are several notable limitations to this study. First, this trial has a risk of social desirability bias in AYA reporting of symptoms, particularly in the CETA treatment arms given their therapeutic relationship with counselors. To combat this risk, we are using a standardized ACASI assessment system to measure symptoms at all time points, administered by research assistants and not by the counselors themselves. Second, this trial is occurring across several urban sites in the capital city of Zambia, and our participants will not be representative of AYA in more rural areas of Zambia and across other rural LMIC settings. Additional research will be needed on the delivery of these interventions to rural populations where T-CETA may actually be more feasible and acceptable because of access to private space and the high costs of transportation to a clinic.

If the CETA technology training platform is deemed feasible and comparably effective to in-person training models, and T-CETA is found to be as effective as in-person CETA for AYA in Zambia, we aim to expand these technology-driven, cost-effective training and treatment delivery methods across several contexts in sub-Saharan Africa and other LMIC globally.

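### The non-inferiority margin is 72% of the plan's own minimum CETA effect, and the T-CETA conclusion is not tied to the planned T-CETA versus TAU test

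*Protocol article*

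**What the plan says.** All design figures are in the protocol article, Methods, Data analysis, and refer to the CPSS.

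- Scale: "we hypothesize a baseline mean value of approximately 19.0 and a standard deviation of 13".
- Superiority: "an expected minimum effect size of each CETA condition compared to TAU of 0.5, we would require 78 persons per arm". For alpha, "we will assume an alpha = 0.025 to account for two comparisons".
- Non-inferiority: "a non-inferiority margin of 4.7, which is equivalent to one-third of the anticipated standard deviation", with alpha 0.05, 80% power and 114 per CETA arm. The reason given is that earlier studies regard differences below one-third of an SD as of no practical importance.
- Structure: each CETA arm is first tested separately against TAU. Then: "Second, we will conduct a non-inferiority analysis in which we will compare the outcomes between the CETA and T-CETA groups". No sentence links the two sets of tests.

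The Discussion makes later expansion depend on a feasible and comparably effective training platform and on whether "T-CETA is found to be as effective as in-person CETA for AYA in Zambia".

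On what is known about CETA, the Abstract says that its effectiveness is untested in this age group and that its evidence comes from other populations. The Background says that no fully powered randomized trial has been done in adolescents.

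**The concern.** A non-inferiority margin should be judged against the benefit it is meant to protect. The plan supplies that benefit but does not use it. It treats 0.5 SD over TAU as the effect worth detecting, and treats a loss of about one-third of an SD as negligible. The second figure is most of the first.

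This could be tolerated if the comparator's effect in the population were well established. Here it is not, so protection has to come from the concurrent TAU arm. The arm exists and the T-CETA versus TAU test is planned, but the non-inferiority conclusion does not use it. As written, T-CETA could be called as effective as CETA on an outcome where it has not been shown better than TAU. That conclusion is one of the triggers for expansion named in the Discussion.

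**Working it through.** **Inputs (Data analysis).** SD 13; minimum effect 0.5; margin 4.7; superiority alpha 0.025 and power 0.80; non-inferiority alpha 0.05 and power 80%; 114 per CETA arm and 78 TAU evaluable; 150/150/100 randomized.

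**Assumptions.** Normal arm means with common SD 13, no clustering or covariate adjustment, superiority tests two-sided, non-inferiority one-sided at 0.05 (the article does not state the side). Results are given for 114/78 and, as the no-attrition limit, 150/100.

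**The plan's own figures.**
- Superiority: n = 2 × (2.241 + 0.842)² / 0.5² = 76.0, so 77, or 78 with the t distribution. The stated 78 is reproduced. This confirms that 0.5 is a standardized effect, i.e. 0.5 × 13 = 6.5 points.
- Non-inferiority: n = 2 × (1.645 + 0.842)² × 13² / 4.7² gives 95 (121 at one-sided 0.025), not 114. A margin of 4.3 gives 114, and 13/3 = 4.33 gives 112. The stated n therefore fits one-third of the SD, but not 4.7 with SD 13. Both margins are carried below.

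**Share of the benefit conceded.** 4.7 / 6.5 = 72%, leaving 1.8 points (0.14 SD) over TAU. With SD/3, 4.33 / 6.5 = 67%.

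**What passing requires.** SE of T-CETA minus CETA = 13 × √(2/114) = 1.72, or 1.50 with 150 per arm. The largest observed deficit that passes is 4.7 − 1.645 × 1.72 = 1.87 points, or 2.23 with 150. That is 29–34% of 6.5.

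**Chance of passing for a true loss L:** Φ((4.7 − L)/SE − 1.645).

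| True loss, CETA effect 6.5 | 114 per arm | 150 per arm |
|---|---|---|
| One-third (2.17) | 43% | 52% |
| One-half (3.25) | 21% | 25% |
| Whole margin (4.7) | 5% | 5% |

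With a margin of 4.33 and 114 per arm, the half-effective T-CETA passes in about 15%.

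**Role of the TAU comparison.** The three contrasts share arms, so joint probabilities come from simulating three independent arm means. With a CETA effect of 6.5 and T-CETA keeping half, consider the trials in which non-inferiority passes and CETA beats TAU. In 29% (114/78) to 31% (150/100) of these, T-CETA has not beaten TAU.

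**Effect of adding T-CETA superiority to TAU as a condition:**

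| Scenario | T-CETA keeps half: 114/78 | T-CETA keeps half: 150/100 | T-CETA equals CETA: 114/78 | T-CETA equals CETA: 150/100 |
|---|---|---|---|---|
| CETA effect 6.5, non-inferiority alone | 21% → 11% | 25% → 15% | 86% → 78% | 93% → 89% |
| CETA effect 6.5, CETA must already beat TAU | 15% → 11% | 22% → 15% | 74% → 71% | 88% → 86% |
| CETA effect 4.7, CETA must already beat TAU | 16% → 9% | 27% → 13.5% | 47% → 40% | 65% → 56% |

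**The case against.** **The safeguard is already planned and will be reported.** This is true: T-CETA is tested against TAU at alpha 0.025, so a T-CETA not shown better than TAU would be visible. The article is also condensed, and a combining rule may stand in the full protocol or analysis plan, which are not shown. Elsewhere the article ties scale-up to both versions being effective (Abstract, Discussion; Study setting), and the sentence on expansion is a future aim, not a decision rule. This lowers the weight of the point. But reporting two results side by side is not a rule for combining them, and the margin with its rationale is fixed in the article itself.

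**A rationale is given, and 0.5 is a minimum.** A larger true effect shrinks the conceded share: at an illustrative 0.8 SD (10.4 points) it is 45%. But one-third of an SD is two-thirds of a 0.5 SD effect by construction, so the practical-importance argument does not answer the question of retained benefit. The trial is also sized to succeed at 0.5.

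**Two stronger readings are tempting, and the documents support neither.**
- A reader might infer that T-CETA could easily be called as effective after losing most of the benefit. The 72% is what the confidence bound must exclude, not a loss that usually passes. A true loss that large passes 5% of the time, and the observed deficit must be no more than 1.9–2.2 points.
- A reader might infer that the plan is incoherent because 4.7 exceeds the smallest significant CETA–TAU difference (4.28 points at 114/78). That sets a limit for a confidence bound against a threshold for an observed difference. Like for like, the largest passing observed deficit (1.87) is well below 4.28. With the margin at 4.33 the two are in any case about equal at 114/78.

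**Conclusion.** The point holds in a limited form. On the plan's own figures the margin concedes 72% of the assumed minimum CETA benefit (67% at SD/3). It is justified only as a fraction of the SD, and the non-inferiority conclusion is not tied to the T-CETA versus TAU test, in a population where CETA's effect is not established.

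The realistic exposure is a T-CETA that keeps two-thirds or half of a 6.5-point benefit and is declared non-inferior in 43–52% or 21–25% of trials. For the half-effective T-CETA, about 30% of the passes in which CETA beats TAU come without T-CETA beating TAU. These figures rest on SD 13, a true CETA effect at the stated minimum, one-sided 0.05 and simple comparisons of arm means. They concern the CPSS, the only outcome for which the article gives figures. A larger CETA effect or a margin of 4.33 reduces the problem but does not remove it. A cheap change of wording is worth making; the design need not be reopened on this account.

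**What to change.** In Data analysis:

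1. State that T-CETA is concluded to be as effective as CETA on an outcome only if (a) the confidence bound for T-CETA versus CETA lies inside the margin and (b) T-CETA is superior to TAU on the same outcome in the planned comparison at alpha 0.025.
2. Report the T-CETA minus TAU and CETA minus TAU effects beside the non-inferiority result, with the share of benefit retained as description.
3. State beside the margin what share of the assumed minimum effect it concedes (72% for 4.7, 67% for SD/3), and reconcile 4.7 with one-third of 13.

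**Cost.** No more participants and no new test. The chance of the full claim for a T-CETA truly equal to CETA falls as in the last table: by 4 to 8 percentage points at a 6.5-point effect, or 2 to 3 if CETA must already beat TAU. The loss is larger if CETA's true effect is only 4.7 points: 7 to 9 percentage points with CETA already required to beat TAU. Without that requirement, the claim cannot exceed T-CETA's own chance of beating TAU, 59–71%, against 86–93% for non-inferiority alone.

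**Limit.** At 6.5 points a half-effective T-CETA still makes the full claim in 11–15% of trials. One that loses a third does so in 28–39% (CETA also beating TAU). Curing the margin itself would need a smaller one. As an illustration, 3.25 points (half the benefit) needs 198 evaluable per CETA arm at one-sided 0.05 and 80% power, or 198 / 0.75 = 264 randomized per arm at 25% attrition.
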